## LIST OF ABBREVIATIONS AND DEFINITIONS OF TERMS

### Abbreviations

|         |                                                         |
|---------|---------------------------------------------------------|
| AI      | artificial intelligence                                 |
| AI-DP   | artificial intelligence digital pathology               |
| CI      | confidence interval                                     |
| eCRF    | electronic case report form                             |
| eDC     | electronic data capture                                 |
| EPG     | eggs per gram                                           |
| FOIA    | Freedom of Information Act                              |
| GPH     | Global Public Health                                    |
| ICF     | informed/assent consent form                            |
| IEC/IRB | Independent Ethics Committee/Institutional Review Board |
| J&J     | Johnson and Johnson                                     |
| KK      | Kato-Katz                                               |
| KK1.0   | Kato-Katz 1.0                                           |
| KK2.0   | KK AI-DP                                                |
| LATAM   | Latin America                                           |
| NTD     | Neglected Tropical Diseases                             |
| PC      | preventive chemotherapy                                 |
| R&D     | Research and Development                                |
| STH     | soil-transmitted helminthiasis                          |
| TSET    | Tube Spontaneous sEdimentation Technique                |
| WHO     | World Health Organization                               |

### Definition of Terms

|                      |                                                                                                                                                                                                                                                                                                                                                             |
|----------------------|-------------------------------------------------------------------------------------------------------------------------------------------------------------------------------------------------------------------------------------------------------------------------------------------------------------------------------------------------------------|
| Study                | The term “study” indicates a non-interventional clinical activity where patient level data may be systematically collected and/or analyzed for medically important results/outcomes, for research purposes. The use of this term in no way implies that any interventional treatments or procedures, planned or otherwise, have been provided or performed. |
| Prospective study    | A study in which the outcome of interest occurs after the research begins.                                                                                                                                                                                                                                                                                  |
| School-aged children | School-aged children that are most susceptible to soil-transmitted helminthiasis.                                                                                                                                                                                                                                                                           |

## 1. INTRODUCTION

### 1.1. Background

Johnson and Johnson (J&J) Global Public Health (GPH) aims to improve access to medicines, foster collaborations, and support public health solutions to sustainably advance healthcare worldwide. Since 2006, J&J has cumulatively donated 2 billion doses of VERMOX (mebendazole) 500 mg tablets to treat intestinal worm infections (also known as soil-transmitted helminthiasis, [STHs]) in children living in STH endemic countries.

With goals of supporting the elimination of STH morbidity as a public health problem, J&J is publicly committed to an annual donation of 200 million doses of chewable mebendazole through 2025. Aligned with the World Health Organization's (WHO) 2030 Neglected Tropical Diseases (NTD) roadmap, J&J GPH is focused on combatting STH infections through donations that aim to decrease STH infection prevalence and reduce STH morbidity. As progress is made against STH, endemic countries can graduate out of donation programs and what little STH burden remains can be incorporated into individual country universal health coverage, where available.

Unification of different NTD stakeholders together, can significantly contribute to the control and elimination of these NTDs. Soil-transmitted helminthiasis control programs are based on a mass drug administration to a target population, regardless of individual infection status – so called preventive chemotherapy (PC) programs. The primary microscopic diagnostic technique to support the WHO programs is known as Kato-Katz (KK) thick-smear, in which stool samples are collected, made into a slide smear, and eggs are counted to determine infection intensity. However, limited local diagnostic capacity to assess the prevalence and intensity of infections in a standardized and timely way, is impacting the evaluation and decision-making processes of drug donation utilization within STH country programs.

This study is an opportunity to support and accelerate the development and data generation of an innovative diagnostic tool that could potentially increase the efficiency and impact of mebendazole drug donation to patients around the world.

Janssen GPH Research and Development (R&D) has been evaluating an artificial intelligence digital pathology (AI-DP) based on the KK thick-smear, to achieve WHO goal for the Diagnostic Target Profile of the STH as part of J&J contribution to 2030 NTD goals. The prototype unit has travelled for demonstration and field testing to Tanzania, Cambodia, Kenya, Ethiopia, Washington DC (COR-NTD Innovation Lab) and Belgium. During the course of evaluation, 7,780 field of view images (of approximately 800  $\mu\text{m}$  x 600  $\mu\text{m}$ ) were manually reviewed to verify image quality, image focus, locations and classes of STH eggs. A total of 16,990 parasite eggs have been marked-up and form the ground truth data for training artificial intelligence (AI) models. An open- source relational database built in MySQL (a database management system) manages the data and allows the custom AI-DP development pipeline.

The performance of the technology is summarized as follows:

- *Ascaris lumbricoides*: Sensitivity 96%, Specificity 98%, Precision 98%, Accuracy 97%
- *Trichuris trichiura*: Sensitivity 97%, Specificity 98%; Precision 93%, Accuracy 98%
- Hookworms (*Necator americanus* and *Ancylostoma duodenale*): Sensitivity 96%, Specificity 99%; Precision 97%, Accuracy 99% [1]

Since the frequency (ie, annually or bi-annually) of drug administration in PC programs are based on prevalence and intensity of infections, the AI-DP tool is a more sensitive diagnostic method and that can lead to more successful implementation of STH programs. The WHO has defined threshold criteria to describe low, moderate and heavy infection intensity and is presented below in [Table 1](#) [2].

**Table 1: Fecal Egg Count Thresholds Defining Low, Moderate and Heavy Infection Intensity [2]. The Fecal Egg Counts are Expressed as Eggs per Gram of Stool.**

|                             | Low     | Moderate     | Heavy   |
|-----------------------------|---------|--------------|---------|
| Ascaris lumbricoides | 1–4,999 | 5,000–49,999 | >50,000 |
| Trichuris trichiura  | 1–999   | 1,000–9,999  | >10,000 |
| Hookworms                   | 1–1,999 | 2,000–3,999  | >4,000  |

The current AI-DP prototype is now ready to be piloted in Latin America (LATAM). Soil-transmitted helminthiasis infect a significant proportion of Latin Americans, particularly in poor neighborhoods and native communities. It is estimated that in LATAM and the Caribbean at least 13.9 million preschool-aged (pre-SAC) and 35.4 million school-aged children (SAC) are at risk of infections by STH [3]. These infections rarely cause death, but their public health consequences are manifest in the chronic, insidious effects that the condition has such as malnutrition, anemia, impeded growth and increased susceptibility to other infections. In both pre- SAC (1-4 years) and SAC (5-14 years), the age-groups most at risk, STH infection stunts physical growth and impairs the development of cognitive function, hampering performance and attendance within the education system and ultimately hindering economic development [4-6]. The recommended control strategy is a population-based approach whereby all members of a target population receive treatment with anthelmintic drugs, usually albendazole or mebendazole, regardless of infection status. This kind of PC known as mass drug administration, is relatively inexpensive and justified as the risks for uninfected individuals receiving the drug is low [7]. However, a diagnostic tool such as the AI-DP can more accurately and efficiently estimate the prevalence of STH infection in LATAM, thus making drugs more readily available to this population through a more targeted donation program.

## 1.2. Current Treatments

Soil-transmitted helminths (STH) include *A. lumbricoides*, *T. trichiura*, and 2 hookworm species, namely *Necator americanus* and *Ancylostoma duodenale* (hence forth will be designated as hookworms). Global estimates indicate that more than 1.5 billion people are infected with at least one of the 4 STH species [8]. They are responsible for an estimated 3.3 million disability- adjusted life years of which 1.2 million occurred in children which is the highest burden among all

NTDs [9]. Preventive chemotherapy is the main strategy to control the morbidity caused by STHs. This entails the periodic administration of a single, oral dose of albendazole (ALB; 400 mg) or mebendazole (MEB; 500 mg) mainly to children through school-based PC program [10].

### 1.3. Overall Rationale for the Study

The validation of the AI-DP tool in LATAM is critical as the region's standard of care for monitoring STH prevalence is Tube Spontaneous sedimentation Technique (TSET, a concentration by sedimentation assay, without centrifugation) which is a qualitative method and differs from the most commonly applied diagnostic method elsewhere, the KK (hence forth will be designated as KK1.0), a quantitative method. The KK1.0 technique is recommended by WHO for helminthiasis diagnosis [5], however limited reproducibility, a low sensitivity for low intensity infections, and the fact that it needs to be performed on fresh samples means that it is not always the ideal method. This may be particularly true in the context of evaluating large scale interventions aimed at STHs, furthermore, the distance to the central laboratory, combined with limited staff availability has led countries to choose concentration techniques over the KK1.0. [11]. Hence, data comparing KK AI-DP (hence forth will be designated as KK2.0) to local approaches is necessary to the evaluation of the tool and to drive future adoption into the LATAM region.

Counting of helminth eggs requires a minimum amount of laboratory equipment and experienced laboratory technicians to ensure quality of the data obtained; and it is essential that samples are analyzed quickly after collection to ensure visualization of hookworm eggs. This has prompted the search for an improved diagnostic method, the KK2.0 technique which uses AI-DP to facilitate egg counts without using a microscope, uses automated egg counting, and submission of results from remote locations, even if no internet connection is available at the data collection location.

## 2. OBJECTIVES AND HYPOTHESIS

### Research Question

The intent of the study is to evaluate the sensitivity of KK2.0 at detecting STH eggs among SAC living in selected STH endemic areas of Ucayali, a remote Amazonian region of Peru.

Since a “gold” standard diagnostic test is not available for detection of intestinal parasites, the operational characteristic (sensitivity) will be estimated using the combined results from KK1.0 and KK2.0 at 30-minute and 24-hour timepoints and TSET (within first hour) (see Objectives below and [Figure 1](#) for schematic flow chart) as a diagnostic pseudo “gold” standard in this study [12].

## Objectives

| Objectives                                                                                                                                                                                                                                                                                                                                                                            | Endpoints                                                                                                                                                                                                                                                                                                                  |
|---------------------------------------------------------------------------------------------------------------------------------------------------------------------------------------------------------------------------------------------------------------------------------------------------------------------------------------------------------------------------------------|----------------------------------------------------------------------------------------------------------------------------------------------------------------------------------------------------------------------------------------------------------------------------------------------------------------------------|
| Primary                                                                                                                                                                                                                                                                                                                                                                        |                                                                                                                                                                                                                                                                                                                            |
| To assess the diagnostic performance of KK2.0 in comparison to KK1.0 at detecting hookworms ( Necator americanus and Ancylostoma duodenale ) and Ascaris lumbricoides and Trichuris trichiura in SAC living in selected areas of Ucayali, a remote Amazonian region of Peru, at the 30-minute and 24-hour timepoints, respectively, of slide preparation. | 
 
Eggs per gram (EPG)
 
Sensitivity of KK1.0 and KK2.0 at 30-minute and 24-hour timepoints
 
Agreement in KK1.0 and KK2.0 results at 30-minute and 24-hour timepoints
 
Percentages of SAC with low, moderate, or heavy intensity of infection by EPG
 
 |
| Secondary                                                                                                                                                                                                                                                                                                                                                                      |                                                                                                                                                                                                                                                                                                                            |
| To evaluate the prevalence STH (hookworms [ Necator americanus and Ancylostoma duodenale ], and Ascaris lumbricoides and Trichuris trichiura ) in the selected endemic, remote Amazonian region of Ucayali, Peru.                                                                                                                                         | 
 
STH prevalence as a percentage in SAC living in the selected areas of Ucayali, Peru
 
                                                                                                                                                                                      |
| Exploratory                                                                                                                                                                                                                                                                                                                                                                    |                                                                                                                                                                                                                                                                                                                            |
| To assess and compare if KK2.0 with KK1.0 and TSET at identifying intestinal parasites, other than STH                                                                                                                                                                                                                                                                                | 
 
Description of intestinal parasites, identified in SAC enrolled in the study
 
                                                                                                                                                                                             |

## Hypothesis

This is a prospective, non-interventional study to evaluate the KK2.0 method and compare its efficiency to KK1.0 at detecting STH. The results will be presented descriptively, the analysis will be exploratory in nature, and no hypotheses are prespecified.

## 3. RESEARCH METHODS

### 3.1. Study Design and Rationale

#### 3.1.1. Overview of Study Design

This is a prospective, non-interventional field study that will be conducted in selected STH endemic areas of Ucayali, a remote Amazonian region of Peru. This trial will evaluate the KK2.0 method and the data collected will aim to advance the goal to strengthen existing STH program surveillance by improving the sensitivity of current testing, and by providing access to timely and higher quality data (more efficient and faster data).

Approximately 2 weeks prior to stool collection, field workers will initially survey the geographical area of Ucayali, Peru, specifically area A, B, C, D, E, and F (refer to map of Ucayali, Peru), to identify homes with SAC, aged 5-14 years (Visit 1). The day prior to sample production and collection, field workers will visit the homes of children in the study population, where they will explain the study to parents/guardians and children over the age of 8, obtain informed consent

from parents/guardians of SAC aged 5-14 years, and additionally an assent from SAC older than 8 years (Visit 2). Participating households will then receive a sample pot to be collected by the field worker the following day.

Field workers will then collect the stool samples from the consented/assented SAC (Visit 3) and take them to the local laboratory site within  $4\pm 1$  hours of collecting the samples. At the laboratory, samples will be processed and analyzed for the presence of *A. lumbricoides*, *T. trichiura*, and hookworm eggs. Results of a STH or other additional parasites identified by TSET (the standard diagnostic method in Peru), will be given to the children's parents/guardians and recommended that they seek treatment.

Within 1 hour of stool sample arriving at the laboratory site, lab technicians will prepare from each sample a TSET assay, and 2 KK thick-smear slides (differentiated as Slide A and Slide B; see [Figure 1](#) for schematic flow chart and Peru KK2.0 Laboratory Protocol for a narrative description). One technician will prepare the sample for TSET and count the number of *A. lumbricoides*, *T. trichiura*, hookworm eggs, and any other additional identifiable parasites. This will provide qualitative data for later analysis. Two other lab technicians, using the same homogenized stool sample, will prepare the 2 KK thick-smear slides, Slide A and Slide B. Slides A and B will be analyzed within the first 30 minutes ( $\pm 10$  minutes) of slide preparation, in order to count hookworm eggs. Hookworm eggs will clear (ie, eggs will hatch) and disappear from stool samples within this window of time. Slide A will be analyzed via the KK1.0 method that uses manual counts of *A. lumbricoides*, *T. trichiura*, hookworm eggs, and any other identifiable parasites in the 30-minutes timeframe, and Slide B via the KK2.0 method that uses automated egg counts. Slide B will be loaded into the AI-DP slide scanner (aka KK2.0 method) and the system will automatically collect images of the slide. An on-board AI program will process the images, identifying eggs for verification. The slide images and identified eggs will be later uploaded to a cloud database and subsequently uploaded to the study database. See KK2.0 AID2STOP User Manual.

Slide B will be refrigerated overnight to allow the sample to become clearer from sediment and debris so that *A. lumbricoides* and *T. trichiura* eggs can be more easily identified. At the  $24\pm 4$ -hour timepoint, Slide B will undergo a manual (KK1.0) and digital (KK2.0) egg count. Slides will be randomly selected for the KK1.0 method first or KK2.0 method second, or vice versa.

All slides read by the KK1.0 method will be converted to eggs per gram (EPG) of stool statistics and uploaded to the study database. The images of all slides scanned into the AI-DP tool will be uploaded to the EggInspector application (see EggInspector Quick Start Guide) in the cloud database which will identify the eggs and the images will be validated by an expert parasitologist in Peru. Validated results will be uploaded to the study database.

Following data collection and upload to the study database, data will undergo quality control, cleaning, and eventually database lock. Ten percent of all slides (ie, KK1.0 and TSET) and 100% of KK2.0 will undergo quality control at each timepoint, where they will be recounted for eggs at the end of the day.

All positively identified specimens for parasites as well as those with negative results by TSET will be summarized at the central laboratory, as per the standard of care in Peru. A signed letterhead by the laboratory's director will be delivered to the children's parents/guardians by the field workers notifying them of their children's infection status (Visit 4) with the recommendation to follow up with their healthcare provider clinic for treatment if positive for any STH or other parasites.

The collection of stool samples will be conducted for approximately 3 months followed by a 2-month period for analysis of results.

The different steps of the trials are schematized in Figure 1.

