#### 3.4.2. Measures of Effectiveness/Clinical Response

##### 3.4.2.1. Effectiveness/Clinical Response Measures

At the laboratory, trained laboratory technicians will prepare stool-thick-smear slides for KK1.0, KK2.0, and stool concentrations for the TSET method and will be read manually and by the KK2.0 method at specific timepoints and in accordance with standard process for each test. Slide images read by the AI-DP tool will be uploaded to the EggInspector application in the cloud database (see EggInspector Quick Start Guide), then manually verified by an expert parasitologist in Peru. Validated results will be uploaded to the study database.

Definitions of appropriate measures of effectiveness/clinical response are as follows:

- KK1.0 method: The microscopy diagnostic standard for diagnosing STH infection intensity. Stool samples are made into a slide smear in which eggs are counted.
- KK2.0 method: An improved diagnostic technique over KK1.0 in development that uses AI-DP technology to facilitate egg counting without using a microscope. Using the KK thick

smear technique, stool slide smear will be inserted into a slide scanner to provide an automated egg count. At present, this is a hybrid methodology that uses AI-DP and an expert parasitologist verification.

- TSET method: A qualitative method commonly used in LATAM to monitor for STH infection using a concentration by sedimentation assay, without centrifugation.
- Positive to any STH result: Any sample with egg(s) of any STH species identified by any of the diagnostic methods.

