### **7.2.3. Data Protection**

#### **Privacy of Personal Data**

The collection and processing of personal data from children enrolled in this study will be limited to those data that are necessary to fulfill the objectives of the study.

These data must be collected and processed with adequate precautions to ensure confidentiality and compliance with applicable data privacy protection laws and regulations. Appropriate technical and organizational measures to protect the personal data against unauthorized disclosures or access, accidental or unlawful destruction, or accidental loss or alteration must be put in place. Sponsor personnel whose responsibilities require access to personal data agree to keep the identity of participating children confidential.

The ICF and assent obtained from the child (or his/her legally acceptable representative) includes explicit consent for the processing of personal data and for study-related data monitoring and Independent Ethics Committee/Institutional Review Board (IEC/IRB) review. This consent also addresses the transfer of the data to other entities and to other countries.

The child's parents/guardians will receive results of positively identified specimens for parasites as well as those with negative results by TSET as it is the standard diagnostic test used in Ucayali central lab and in Peru to diagnose parasitic infections. Field workers will recommend to the child's parents/guardians to have their children followed up with their healthcare provider clinic for treatment if positive to any STH or other parasites.

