**QC (10 % at Random)****Day 1**

**Sedimentation (00 Hrs) [+ (2-5)/ ++ (6-10) / +++ (> 10)] (MARK only: 1, 2 or 3)**

\* Hookworm= Ancylostoma/Necator

[figure not shown]

Negative  
Yes

|   |                            |   |                            |   |                            |   |                            |   |                            |   |                            |          |                            |   |                            |   |                            |    |                            |
|---|----------------------------|---|----------------------------|---|----------------------------|---|----------------------------|---|----------------------------|---|----------------------------|----------|----------------------------|---|----------------------------|---|----------------------------|----|----------------------------|
| 1 | Ascari
s                | 2 | Trichuris                  | 3 | Hookwor
m *             | 4 | E.
vermicu
laris     | 5 | H.
nana                 | 6 | H.
diminut
a         | 7        | Taenia                     | 8 | Fasciol
a               | 9 | S.
stercoral
is      | 10 | Giardia                    |
|   |  + |   |  + |   |  + |   |  + |   |  + |   |  + |          |  + |   |  + |   |  + |    |  + |
| 1 | Capilla
ria sp          | 1 | D.
pacificum            | 1 | Trichostro
ngylus       | 1 |                            | 1 |                            | 1 |                            | Comments |                            |   |                            |   |                            |    |                            |
|   |  + |   |  + |   |  + |   |  + |   |  + |   |  + |          |                            |   |                            |   |                            |    |                            |

**SLIDE A - KK1.0 (30 + - 10 min)  
(All Parasites Egg N°)**

| Factor |   |   |
|--------|---|---|
| 8      | 1 | 2 |
|        | 2 | 4 |

| Stool
TYP
E |
|-------------------|
|                   |

1= Normal, formed  
(24)  
2 = Pasty (12)  
3= NO N- LIQUID  

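### The protocol names TSET as the basis for results returned to families and has no rule for a child who is positive on a manual KK1.0 read but TSET negative, so that child may receive a negative infection status and no referral

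*Protocol*

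**What the plan says.** **What families receive.** Section 3.1.1, like the Synopsis (Study Design), states: "Results of a STH or other additional parasites identified by TSET (the standard diagnostic method in Peru), will be given to the" parents or guardians, with advice to seek treatment. Later in the same section, positive specimens and those negative by TSET "will be summarized at the central laboratory, as per the standard of care in Peru". A letter signed by the laboratory director then tells the family the child's "infection status (Visit 4) with the recommendation to follow up with their healthcare provider clinic for treatment if positive for any STH" or other parasites. Section 7.2.3 says parents receive positive findings and "those with negative results by TSET as it is the standard diagnostic test used in Ucayali central lab" and in Peru. The Data Collection Schedule lists delivery of stool results at Visit 4 without naming a method. Its footnote ties treatment recommendations to regional standard of care.

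**What the study reads.** Section 3.1.1 plans one TSET per sample, a manual KK1.0 read of Slide A at 30 minutes, and a manual KK1.0 read of Slide B at 24±4 hours, beside the KK2.0 scans.

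**How the study regards KK1.0.** Section 1.3: "The KK1.0 technique is recommended by WHO for helminthiasis diagnosis". Section 3.4.2.1 defines it as "The microscopy diagnostic standard for diagnosing STH infection intensity".

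**Who counts as positive.** Section 3.4.2.1 defines a positive STH result as "Any sample with egg(s) of any STH species identified by any of the diagnostic methods". Section 4.3.1 treats a sample as truly positive if any method is positive at any time, and counts a child positive at any time as STH infected.

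**The concern.** The protocol answers the question of whether a child is infected in two ways. For families, the only method named is TSET. For the analysis, any method suffices. The analysis rule does not govern notification, so the two can differ legitimately. It does show that the study will hold the contrary result.

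A child with eggs on a manual slide and a negative TSET falls between the two, and no visible text says what happens. The study could hold an egg-positive reading by an established manual method while the family holds a signed negative status and no advice to see a clinic. Recent treatment does not cover the gap, since Section 3.3.1 excludes children treated with an anthelmintic in the previous 90 days. Mass treatment regardless of infection status (Section 1.1) may reach the child later, which limits the harm.

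This concerns the care of participants. No estimate, test or endpoint depends on it.

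**Working it through.** The protocol states no figure on this point, so there is none to reproduce. The check is mainly a comparison of text.

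**1. Which method feeds the letter?**
- Synopsis (Study Design) and Section 3.1.1: the results given to parents are those identified by TSET.
- Section 3.1.1, later paragraph: positive specimens (no method named) and TSET negatives are summarised following standard of care.
- Section 7.2.3: the same pairing, justified by TSET being the local standard test.
- Data Collection Schedule: no method named.

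TSET is the only method named anywhere as the source of a returned result. A KK1.0 or KK2.0 result is never mentioned as going to a family.

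**2. What happens to a child with KK1.0 positive and TSET negative?** If the letter follows TSET, the status is negative and the referral condition is not met. If positive specimens include those found by any method, the child is referred, but the same specimen is also among the TSET negatives to be summarised. The text does not resolve the clash on either reading.

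**3. Would the study know?** Inputs: 500 children (Section 4.1); two manual KK1.0 reads and one TSET per sample (Section 3.1.1).
- Manual KK1.0 reads: 500 × 2 = 1,000.
- TSET reads: 500 × 1 = 500.

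The Sample Processing Form (Attachment 1) has fields for both manual reads. Any egg makes a slide positive. With the form's stool factors, one egg is 1 × 24 = 24 EPG (formed), 1 × 12 = 12 EPG (pasty) or 1 × 8 = 8 EPG (non-liquid diarrhea).

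**4. How many children?** This cannot be derived. Per percentage point of all children who are manual KK1.0 positive and TSET negative: 500 × 0.01 = 5. Purely as an illustration, with values that are not in the protocol:
- prevalence 20%, and 5% of infected children discordant in this way: 500 × 0.20 × 0.05 = 5;
- prevalence 50%, and 20% discordant: 500 × 0.50 × 0.20 = 50.

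The true number could be zero.

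**5. When is the last manual read available?** 24 + 4 = 28 h after slide preparation, at the latest. The Data Collection Schedule gives Visit 4 no date, so whether waiting for this read delays the letter cannot be judged.

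**The case against.** **Returning TSET is a stated and reasoned choice.** It is the local standard of care, and Section 3.4 asks that contact with children accord with clinical practice. This stands as a reason to return TSET. It does not explain leaving out eggs seen on a manual slide, nor calling a one-test negative an infection status when Section 2 says no gold standard exists.

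**KK1.0 is imperfect.** Section 1.3 goes on to cite limited reproducibility and low sensitivity for light infections. Section 3.4.2.1 calls KK1.0 the standard for intensity specifically, and only 10% of KK1.0 slides are recounted. These are fair cautions, but the protocol does not name false positives as a weakness of the method.

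**A reader might infer that such a child is certainly told negative.** The documents do not go that far. Positive specimens are mentioned without a method, the Data Collection Schedule is not limited to TSET, and Section 3.4.2.1 defines a positive result by any method. No sentence says that only TSET results are returned. The letter and consent texts, Figure 1 and the Peru laboratory protocol are not available and may settle the matter.

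**A reader might also infer that a single egg on TSET is recorded as negative.** The quality-control part of Attachment 1 shows "Sedimentation (00 Hrs) [+ (2-5)/ ++ (6-10) / +++ (> 10)] (MARK only: 1, 2 or 3", so the lowest grade starts at 2. No unit is given, the main TSET block of the form is only partly legible, and Section 3.1.1 has the technician count eggs. This is at most one possible route to discordance.

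**Reporting KK1.0 but not KK2.0 could look inconsistent.** KK2.0 readings are verified by an expert parasitologist and recounted in full (Section 3.1.1), which is more checking than KK1.0 receives. Being in development is a thin reason to withhold them, so the sponsor should decide this explicitly.

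**Conclusion.** The point holds as a gap in the reporting rule. TSET is the only named basis for returned results, the letter is described as an infection status with referral only if positive, and no visible text handles a child with KK1.0 positive and TSET negative. On the most natural reading, that child may receive a negative status and no referral, although the study holds a positive manual reading and counts the child as infected.

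This rests on the visible protocol alone and on reading the Section 3.1.1 statement about TSET together with the reason given in Section 7.2.3. The size is unknown and could be zero, and the 5 to 50 children above depend wholly on assumed inputs. No endpoint is affected. It is a cheap improvement for participants. Confidence is medium, because the outcome for the child is inferred.

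**What to change.** **Preferred.** In the Synopsis (both Study Design paragraphs on results), the Data Collection Schedule, Section 3.1.1 (both paragraphs on results) and Section 7.2.3, state that a child positive for any STH or other parasite by TSET, or by any manual KK1.0 read of Slide A or Slide B, is reported as positive and advised to attend the clinic. Issue the letter after the Day 2 manual read. State also whether expert-verified positives by KK2.0 alone are reported, and why.

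**Minimum, if TSET-only reporting is kept.** Describe the content of the letter as the *TSET result* rather than the child's *infection status*, and say that a negative TSET does not exclude infection.

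Either way, align the letter and consent texts if they do not already say this.

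**Cost.** A protocol amendment with ethics approval where applicable (Section 8.1). The preferred change needs no new reading or form field, since both manual reads are already planned and recorded. The letter would have to wait for the Slide B manual read, due by 28 h after slide preparation. Somewhat more families would be advised to see a clinic; Section 1.1 describes the drug's risk to uninfected people as low. The minimum change adds no referrals and no wait.
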